### Intervention

The treatment intervention, CLP, consists of four sessions lasting 60–90 min administered to couples by a trained bilingual facilitator. Session content, scenarios, and examples will be adapted to each couple’s unique circumstances and HIV serostatus. During session one, couples will examine how cultural values (e.g., machismo) and couples’ dynamics and context impact sexual risks and health behaviors. In addition to providing basic information about HIV and AIDS, sexually transmitted infections (STIs), and substance use, couples are introduced to problem solving, the concept of couple’s self-care, and new prevention methods such as PrEP, while stressing those most relevant to the couple’s HIV status. At the end of session one, couples are asked to complete an assignment designed to enhance personal and couple-oriented self-care.

During session two, couples will be introduced to effective communication and goal setting skills, emphasizing how these skills relate to safer sex decision-making in order to increase motivation to utilize different prevention tools. Using examples relevant to the couple, the facilitator will use problem solving techniques to help the couple evaluate different prevention approaches and determine the most appropriate tools to incorporate into the couple’s risk reduction plan. Couples will be strongly encouraged to practice using at least one prevention tool in the coming week as part of their goal-setting and homework assignment.

In session three, couples will explore strategies for strengthening their relationships by (1) identifying and defining unwritten rules, (2) exploring the couple’s power and decision-making process, (3) examining triggers and influences leading to risky sexual behavior, and (4) developing action plans to increase sexual safety. The session incorporates skill-building roleplay scenarios for negotiating HIV-protected sex and exploring different prevention alternatives. By the end of the third session, couples are prompted to develop a couple-oriented relationship strengthening plan that includes alternative ways to practice safer and fun sex.

In the final session, facilitators will guide couples in identifying social support networks and resources for individuals living with HIV, within and outside the Latino and LGBTQ communities that could help attain their established goals. They will also review and refine their plans for engaging in HIV-protected sex, learn strategies for dealing with barriers to goal progress, and review key skills developed during the sessions. The session concludes with a “graduation” ceremony, during which couples make a commitment to follow the plan they developed.

### Control intervention

The comparison intervention is an attention-control (same duration and couple modality), four-session Wellness Promotion intervention [7] adapted to a Latino cultural context. Wellness Promotion focuses on identifying useful services, becoming accurate appraisers of reputable healthcare information from the internet and other sources, and advocating for equitable treatment and services from professionals. It is informational in nature and less interactive than CLP. It also contains ethically required information regarding HIV and STI prevention, including information and referral for PrEP, HIV-testing recommendations, as well as engagement in care and the importance of treatment adherence for HIV-positive participants.

### Quality assurance (QA) and fidelity monitoring

A variety of methods will be employed for QA and to ensure facilitator fidelity to the interventions. All sessions will be recorded using digital audio recorders; after each facilitator delivers a total of eight sessions, a random sample of 20% of each facilitator’s sessions for both conditions will be reviewed by a QA monitor. Upon review of session audio tapes, QA monitors will complete a QA Treatment Rating Form to assess facilitator fidelity with attention to time spent on each activity, adequacy of content delivery, occurrences and nature of treatment contamination, and clinical dynamics (e.g., relative balance of participation between partners). QA data are reviewed, processed, and addressed/troubleshot during regular facilitator supervision.

If QA data for a facilitator is found to fall in the insufficient range after attempting to rectify the problem, the facilitator will not be assigned new couples (but will continue with existing couples to ensure continuity for participants with all recordings reviewed) until the facilitator has successfully re-completed facilitator training. Any detected instance(s) of contamination by facilitators (i.e., overlap between conditions) or improperly handled responses to participants bringing up information from the other intervention will trigger immediate corrective action.

At the end of each session, facilitators will be required to complete a facilitator checklist to record attendance, the extent to which content was covered, time spent on each activity, whether unplanned content was introduced, and whether such content overlaps with the other condition. Additionally, participants will complete a Participant Feedback and Satisfaction form to elicit the extent to which participants experienced the facilitator as competent and the session as helpful, and to assess participants’ overall satisfaction with each session. Participants will also report the nature and frequency of contact with other study participants and whether they have been exposed to information from the other study arm; any evidence of contamination resulting from feedback forms, facilitator checklists, or issues raised in facilitator supervision meetings will be addressed immediately.

### Measures

Assessments will occur at baseline and 3 and 6 months post-intervention; assessments will be interviewer-administered and conducted at the individual level to ensure confidentiality.

#### Primary outcome: HIV-protected acts

The primary outcome, proportion of HIV-protected anal sex acts, will be assessed using a comprehensive risk behavior assessment that is adapted to the couple’s serostatus and use of prevention tools. Our team has developed an algorithm that incorporates three types of protective behaviors, namely (1) condom use, (2) PrEP utilization and adherence for those who are HIV negative, and (3) viral suppression (TasP) and antiretroviral treatment adherence for those who are HIV positive. In addition, the algorithm considers three additional elements, namely (1) couple’s HIV status (HIV negative seroconcordant, HIV positive seroconcordant, and serodiscordant), (2) whether either partner has had sex outside the relationship in the past 3 months, and (3) whether the couple reports 100% condom use with their main partner in the same period. Operationalization of HIV-protected sex acts is detailed in Table 2.

**Table 2 Tab2:** Operationalization of HIV-protected sex acts based on couple’s serostatus, Connecting Latinos en Pareja (CLP), 2017

Algorithm for defining HIV-protected acts with main partner for participants reporting less than 100% condom use with main partner		
HIV status	No casual partners in last 3 months	One or both partners have casual partners
Seroconcordant negative	HIV protected	Both partners adherent to PrEP = protected
		Partner(s) having casual sex are/is adherent to PrEP = protected
Seroconcordant positive	Both adherent to antiretroviral therapy (ARV) and virally suppressed = protected	Both adherent to ARV and virally suppressed = protected
Serodiscordant	HIV-positive partner is virally suppressed and ARV adherent = protected	HIV-positive partner is having casual sex, is adherent to ARV and virally suppressed = protected
	HIV-negative partner adherent to PrEP = protected	HIV-negative partner is having casual sex and is adherent to PrEP = protected

Sexual behavior will be assessed separately for main male partners and casual male and female partners, if applicable. We will classify 100% condom use for anal insertive or anal receptive with main partner in the last 3 months as HIV-protected acts. For participants who report less than 100% condom use, we will assess whether those sex acts that were not protected by condoms were protected by PrEP (for HIV-negative seroconcordant or serodiscordant couples) or TasP (for HIV-positive seroconcordant or serodiscordant couples). Although the intervention is delivered at the dyad level, sexual risk will be assessed at the individual level, given the possibility that some couples who completed the intervention may not be together at either follow-up. Thus, assessments of sexual risk with primary partners will measure sexual behavior with participants’ current primary partner, whether or not this is the same partner who completed the intervention.

Among participants who report viral suppression or use of PrEP, medication adherence will be assessed by multiple measures to confirm the high probability of maintained viral suppression or PrEP protection, respectively, across those sex acts not protected by condom use. These measures include missed dose counts, a visual analog scale [12], and validated AIDS Clinical Trials Group adherence measures [13]. Although these assessments are based on self-report rather than biomarkers (i.e., viral load tests to confirm sustained viral suppression, blood tests to assess antiretroviral adherence), the proposed algorithm provides a comprehensive conceptualization of HIV protection that incorporates currently available prevention approaches.

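### For serodiscordant couples with casual partners, Table 2 credits suppression or PrEP only to the man having outside sex, so the same medication is scored differently and more outside sex can restore a protected score

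*Protocol article*

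**What the plan says.** The section on the primary outcome in the protocol article states: "The primary outcome, proportion of HIV-protected anal sex acts, will be assessed using a comprehensive risk behavior assessment". It refers the reader to Table 2 for the definition of a protected act. The table is headed "Algorithm for defining HIV-protected acts with main partner for participants reporting less than 100% condom use with main partner", so it governs main-partner acts when condom use is incomplete.

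In the serodiscordant row, the column for couples without casual partners has two lines: "HIV-positive partner is virally suppressed and ARV adherent = protected" and "HIV-negative partner adherent to PrEP = protected". Under "One or both partners have casual partners", the two lines become "HIV-positive partner is having casual sex, is adherent to ARV and virally suppressed = protected" and "HIV-negative partner is having casual sex and is adherent to PrEP = protected".

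The text above the table lists outside sex by either man as one of the elements the algorithm takes into account. The text below the table says that acts without a condom will be assessed as to whether they were "protected by PrEP (for HIV-negative seroconcordant or serodiscordant couples) or TasP (for HIV-positive seroconcordant or serodiscordant couples"). That sentence does not mention casual partners.

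**The concern.** The outcome is protection of acts within the couple. In a serodiscordant couple the main-partner exposure is already present. Whether suppression or PrEP covers that exposure does not depend on which man has sex elsewhere. The casual-partner cell nevertheless makes the credit depend on exactly that. Followed literally, it gives no credit for a suppressed HIV-positive partner when only his HIV-negative partner has outside sex. It also gives no credit for a PrEP-adherent HIV-negative partner when only the HIV-positive partner has outside sex.

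Two things are at stake. First, a couple's score on the primary outcome can change because the casual-partner pattern changed while protection between the two men did not, and in one direction more outside sex improves the score. Second, the cell does not say how its two lines combine, so two competent programmers could produce different primary-outcome variables from the same data.

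**Working it through.** The article gives no figure to reproduce here, because the check is one of logic.

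**Inputs, all from Table 2, serodiscordant row, condom use below 100%:**
- S: the HIV-positive partner is suppressed and ARV adherent.
- P: the HIV-negative partner is PrEP adherent.
- C+ and C-: the HIV-positive or the HIV-negative partner, respectively, has casual sex.

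**Rules:**
- No casual partners: protected if S or P. Each line carries its own protected result, so each is sufficient.
- Casual partners, reading A (each line sufficient, as in the adjacent column): (C+ and S) or (C- and P).
- Casual partners, reading B (every man with casual sex must be covered): (if C+ then S) and (if C- then P). The seroconcordant-negative row of the same column expresses this rule.

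There are 4 medication patterns and 4 casual-sex patterns, so 16 states. Of these, 4 x 3 = 12 involve casual sex. In the table, Y is protected and N is not protected. In the casual-sex columns the first letter is reading A and the second is reading B.

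| Medication | No casual sex | Negative partner only | Positive partner only | Both |
|---|---|---|---|---|
| S=0, P=0 | N | N / N | N / N | N / N |
| S=0, P=1 | Y | Y / Y | N / N | Y / N |
| S=1, P=0 | Y | N / N | Y / Y | Y / N |
| S=1, P=1 | Y | Y / Y | Y / Y | Y / Y |

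**Results:**
- Reading A: 2 of 12 states differ from the no-casual score for the same medication. They are S=0, P=1 with only the positive partner having casual sex, and S=1, P=0 with only the negative partner having casual sex.
- Reading A, adding casual sex with medication unchanged: there are 2 switches from not protected to protected. Each of the two states above becomes protected when the other man also has casual sex.
- Reading B: 4 of 12 states differ (the same two, plus both men having casual sex with only one of them covered). There are 0 switches from not protected to protected.
- A against B: they disagree in 2 of 12 states, both in the last column.

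**Two further readings, for completeness:**
- Requiring both lines literally, (C+ and S) and (C- and P), gives 8 differing states and 2 switches. In those switches a couple with both men covered is not protected while one man has casual sex, and protected once both do.
- Treating the casual-sex clause as descriptive only, so that S or P suffices, gives 0 differing states and 0 switches.

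Thus every reading that gives the clause any effect scores identical medication differently from the no-casual column. The reversal with added casual sex occurs on reading A and on the literal both-lines reading, but not on reading B.

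**The case against.** **Outside sex was deliberately built into the algorithm.** This stands. The text above Table 2 declares it as an element, so a score that depends on casual partners is not an error in itself. The 4 differing states under reading B could follow from a choice to count outside exposure.

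**The reversal depends on the reading.** This also stands. Reading B removes it, and the seroconcordant-negative row in the same column is worded that way. The serodiscordant row, however, is not. Its two lines are separate, each with its own protected result and no connective between them, and they mirror two lines that are plainly alternatives in the adjacent column. So the literal rule misbehaves, and the charitable rule has to be imported from another row.

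**A reader might infer that the text below the table contradicts it.** The article does not support this. That sentence names which biomedical method is relevant to which serostatus group, as a summary. It is equally silent about casual partners for seroconcordant-negative couples, where the table clearly uses them. It neither contradicts the cell nor settles its meaning.

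**A reader might infer a bias toward zero of a stated size.** For example, if 5 to 10% of couples fell in the affected states (an assumption) and each moved from 30% to 100%, an arm mean would move by 0.05 x 70 = 3.5 to 0.10 x 70 = 7 points, against the planned difference of 12. This does not carry over to the treatment effect:
- The article gives no share of serodiscordant couples or of these states. The 30% is the assumed pre-intervention proportion of protected acts overall, not the condom proportion in this group.
- The same rule scores both arms. With affected shares f1 and f0 and condom proportion c in both arms, the distortion of the contrast is (f1 - f0) x (1 - c), which is zero when the shares are equal.
- The direction is open. PrEP uptake by the negative partner earns no credit if only an unsuppressed positive partner has casual sex, which would hide an effect. But if the only man with casual sex stops, the couple moves to the no-casual column and gains credit without any change in medication.
- Uptake is not scored as a failure. Such a couple keeps its condom-protected acts and merely gets no credit for the rest.

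**Conclusion.** The point holds as a defect in one cell of the primary-outcome definition. Under the reading that matches the adjacent column, 2 of 12 casual-partner states are scored against the same medication's no-casual score, and both return to protected when more outside sex is added. Under the alternative reading the reversal disappears, 4 states differ, and the two codings disagree in 2 states. This is more than detail left to a fuller document, because the article presents Table 2 as the operational definition, and the rule it states misbehaves if followed literally.

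The conclusion rests only on the wording of the table and on the outcome being main-partner acts. It applies only to serodiscordant couples with casual partners and less than complete condom use. How many couples that is, and whether the between-arm contrast is biased and in which direction, cannot be determined from the article. The point is therefore not evidence that the trial's effect estimate will be attenuated.

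**What to change.** Before outcome data are seen by arm, replace the serodiscordant casual-partner cell with an explicit truth table over suppression with ARV adherence, PrEP adherence, and who has casual sex (positive partner only, negative partner only, both). Require that adding casual sex with medication unchanged can never turn not protected into protected.

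Because the outcome is acts with the main partner, the natural primary scoring is that either route protects, as in the no-casual column; this leaves 0 differing states and 0 switches. If the investigators want outside exposure to count, the rule that every man with casual sex must be covered can be a named sensitivity analysis. It also has 0 switches, and its 4 differing states would then be a stated choice. Align the sentence below Table 2 with whichever rule is adopted, and apply the same code at baseline, 3 months and 6 months.

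The cost is recoding of the collected data plus one sensitivity analysis. The change affects only how acts are scored, not the care or advice given to participants.

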#### Secondary outcomes

Secondary outcomes include HIV protection with male partners outside of the couple relationship (often referred to in the literature as ‘casual’ partners), chlamydia and gonorrhea infection, use of other HIV risk reduction strategies such as sero-sorting and strategic positioning, and smoking, alcohol, and other substance use. To assess HIV protection among casual male partners, we will ask participants the number of casual male partners in the last 3 months. To minimize recall bias, we will focus on the last anal sex encounter with a casual partner. Participants will report the type of anal sex and whether or not a condom was used from start to finish; we will also assess if it was protected via PrEP or TasP, and the self-reported HIV status of the casual partner. If the casual partner is HIV positive, we will ask if the partner is on treatment and if he is virally suppressed.

For those who consent to optional HIV and STI testing, we will test for current chlamydia and/or gonorrhea infection. Participants will be asked to collect a urine sample, throat swab, and rectal swab to detect genital, oral, and rectal infection, respectively. Those consenting to HIV and STI testing will also be tested for HIV by certified testers at the study site using a rapid HIV test.

We will also capture more informal HIV sexual risk reduction strategies, such as strategic positioning (choosing sex role in anal intercourse based on partners’ serostatus) and serosorting (selecting partners with concordant serostatus). Utilization of these risk reduction strategies will be assessed using a five-item, self-reported questionnaire that includes questions such as, “*In the past ninety days, did you intentionally have sex only with HIV-negative partners in order to reduce the risk of becoming infected with HIV?*” (if HIV negative) and, “*In the past ninety days, to reduce risk, did you only have insertive sex (i.e. you were the top) with HIV-positive men?*”

Smoking, alcohol, and substance use will be assessed using the 12-item Substance Use Inventory [14], a validated measure that assesses tobacco, alcohol, and illicit drug use in the participant’s lifetime and within the preceding 30 and 90 days.

#### Other measures

Further measures will assess social cognitive factors, relationship-oriented ecological factors, and cultural and environmental factors that influence HIV risk or potentially moderate or mediate intervention effects. The majority of the measures are comprised of or based on validated scales that have been previously used in studies with Latino MSM, black MSM and/or previous research with couples. A complete list of study measures is outlined in Fig. 2.

**Fig. 2 Fig2:**
[figure not shown]
Schedule of enrolment, interventions, and assessments

### Data collection

All study data will be collected electronically using REDCap, a software application designed to build online surveys and databases. REDCap provides numerous safeguards against confidentiality breaches and is designed to comply with HIPAA, 21 CFR part 11 and FISMA regulations. Upon completion of assessments, data are automatically uploaded to a secure, password-protected cloud database; participant assessment data are not linked to identifying information. Data gathered from REDCap may be seamlessly imported into statistical software packages for subsequent data analysis.

### Data analysis

Initial data analysis tasks will involve univariate and bivariate statistics to characterize the sample and review the distributional properties of measures across treatment arms. To evaluate the efficacy of the intervention, we will use random effect models and/or generalized estimating equations (GEE) modeling 6-month follow-up differences, adjusting for characteristics at baseline, 3-months, and treatment arm in order to increase statistical precision. GEE models will consistently be used in cases where unobserved heterogeneity invalidates the application of random effect models. Additional covariates will be included as indicated by comparison of baseline differences and variables of theoretical importance (e.g., serostatus concordance). We will also explicitly test baseline × treatment interactions. We expect to model our main outcome as a continuous variable, but based upon examination of pilot data, some adjustment for interval censoring (i.e., considerable proportions reporting condom use on all or no occasions) may be required in order to meet distributional assumptions.

Following evaluation of Aim 2, we will perform a set of exploratory analyses to develop dyadic models for sero-discordant couples in which partners are not exchangeable in terms of risk [15]. We will also explore factors associated with the magnitude of treatment effects (i.e., potential moderators) as well as potential mediators. Effect modification will be evaluated directly through random effects models or as multiplicative composites in GEE models. Hypothesis testing will implement an intention-to-treat approach. We will employ GEE to account for the non-independence in measures arising from (1) “autocorrelation”, due to repeated measures with the same person, and (2) “intraclass correlation”, arising from partners in a dyad who are reporting on behaviors conjoint within that dyad.

